# Comparison of total parathyroidectomy without autotransplantation and without thymectomy versus total parathyroidectomy with autotransplantation and with thymectomy for secondary hyperparathyroidism: TOPAR PILOT-Trial

**DOI:** 10.1186/1745-6215-8-22

**Published:** 2007-09-18

## Abstract

**Background:**

Secondary hyperparathyroidism (sHPT) is common in patients with chronic renal failure. Despite the initiation of new therapeutic agents, several patients will require parathyroidectomy (PTX). Total PTX with autotransplantation of parathyroid tissue (TPTX+AT) and subtotal parathyroidectomy (SPTX) are currently considered as standard surgical procedures in the treatment of sHPT. Recurrencerates after TPTX+AT or SPTX are between 10% and 12% (median follow up: 36 months).

Recent retrospective studies demonstrated a lower rate of recurrent sHPT of 0–4% after PTX without autotransplantation and thymectomy (TPTX) with no higher morbidity when compared to the standard procedures. The observed superiority of TPTX is flawed due to different definitions of outcomes, varying follow up periods and different surgical treatment strategies (with and without thymectomy).

**Methods/Design:**

Patients with sHPT (intact parathyroid hormone > 10 times above the upper limit of normal) on long term dialysis (>12 months) will be randomized either to TPTX or TPTX+AT and followed for 36 months. Outcome parameters are recurrence rates of sHPT, frequencies of reoperations due to refractory hypoparathyroidism or recurrent/persistent hyperparathyroidism, postoperative morbidity and mortality and quality of life. 50 patients per group will be randomized in order to obtain relevant frequencies of outcome parameters that will form the basis for a large scale confirmatory multicentred randomized controlled trial.

**Discussion:**

sHPT is a disease with a high incidence in patients with chronic renal failure. Even a small difference in outcomes will be of clinical relevance. To assess sufficient data about the rate of recurrent sHPT after both methods, a multicentred, randomized controlled trial (MRCT) under standardized conditions is mandatory.

Due to the existing uncertainties the calculated number of patients necessary in each treatment arm (n > 4000) makes it impossible to perform this study as a confirmatory trial. Therefore estimates of different outcomes are performed using a pilot MRCT comparing 50 versus 50 randomized patients in order to establish a hypothesis that can be tested thereafter.

If TPTX proves to have a lower rate of recurrent sHPT, no relevant disadvantages and no higher morbidity than TPTX+AT, current surgical practice may be changed.

**Trial registration:**

International Standard Randomized Controlled Trial Number Registration (ISRCTN86202793)

## Background

### Medical problem

Secondary hyperparathyroidism (sHPT) is common in patients with chronic renal failure, affecting most of those who are receiving hemodialysis [1,2]. Overall 60.992 patients were treated with continuous haemodialysis for renal failure in Germany 2004. The annual increase of 3% in patients requiring haemodialysis appears constant within the last years [3].

Renal insufficiency leads to a reduced synthesis of 1,25-dihydroxy-Vitamin D secretion and a decrease in phosphate excretion resulting in hypocalcemia and hyperphospatemia. Consecutively, parathyroid hormone secretion and parathyroid cell hyperplasia increases. With time, sHPT is characterized by persistently elevated levels of intact parathyroid hormone (PTH) above the desired target range recommended by the Kidney Disease Outcomes Quality Initiative (KDOQI [4]) and complicated by important disturbances in mineral metabolism and skeletal resistance to the calcemic actions of parathyroid hormone [5-7]. Renal osteopathy is the most widely recognized consequence of sHPT.

However, several reports indicate, that alterations in calcium and phosphorus metabolism, as a result of either sHPT or the therapeutic measures used to manage it, contribute to soft-tissue and vascular calcification, cardiovascular disease, and the risk of death [8-12].

Episodes of hypercalcemia and hyperphosphatemia are often aggravated by the use of calcium as a phosphate-binding agent, particularly in combination with Vitamin D sterols, which increase the absorption of calcium and phosphorus [12-15]. Recently, several new agents including calcimimetics [16,17], new phosphate binders [18] and less calcemic vitamin D analogues [19-22], have been added to the list of therapeutic modalities in the management of sHPT.

Despite the advent of these new therapeutic agents, patients with long-standing sHPT often require parathyroidectomy. The indication for surgery depends on clinical symptoms of progressive renal osteopathy and impaired calcemic response following PTH secretion in the absence of Vitamin D deficiency: either if hypercalcemia develops (spontaneously or under treatment with Vitamin D), if the new therapeutic modalities fail to control sHPT or if medical therapy has to be adjourned because of adverse reactions. However, the rate of parathyroidectomies (PTX) did not change significantly between 1991 and 2001 despite the progression in medical therapy with phosphate binders and Vitamin D analogues [23].

Overall PTX is required in about 20% of patients after 3–10 years of dialysis and up to 40% after 20 years [24,25].

### Current treatment options

Three different surgical procedures are reported in the literature following the first PTX for secondary HPT in 1960 [26]: subtotal PTX (removal of three and a half glands and leaving half of a gland as a remnant in the neck [27,28], total PTX with autotransplantation (TPTX+AT) of some of the excised tissue into defined areas (forearm muscle, anterior tibial muscle or subcutaneously [28-31], and total parathyroidectomy without autotransplantation (TPTX) [32,33]. Ogg [34] initially reported that TPTX provides a feasible therapeutic option in patients who are on chronic dialysis therapy. However, TPTX was not introduced into clinical practice because of the potential complication of adynamic bone disease or severe ongoing hypocalcemia. Therefore subtotal PTX or TPTX+AT, both supplemented with thymectomy, are currently considered as the standard procedures in the treatment of sHPT [28,32,35,36].

However, both procedures leave a fragment of activated, proliferated parathyroid tissue, though at different sites. Since the pathophysiological condition of chronic renal failure and maintenance dialysis continues, the growth stimulus persists and may cause recurrent sHPT at the site of the remnant. Although relapse of HPT has been observed at different intervals after initial surgery, it is quite clear that the incidence of recurrent disease increases with time [37,38]. A wide range of recurrence rates has been published for both procedures (range 5–80%). This variation is dependent on the definition of recurrent sHPT and variability in follow up periods given in different series for both techniques [32]. Recurrence-rates after TPTX+AT or subtotal PTX after a median follow up of 36 months are reported to be between 10% and 12% [31,39-41]. All other clinically relevant outcome parameters (mortality and morbidity) do not differ significantly between TPTX+AT and subtotal PTX [28,40,42].

The site of recurrence in patients after TPTX+AT is located in approximately 80% at the graft (Figure 1) and in 20% in the neck [24,36,43-47].

**Figure 1 F1:**
[figure not shown]
This figure shows the enlargement of a parathyroid autograft in a patient with recurrent secondary hyperparathyroidism, demonstrated by a knob underneath the scar.

Graft-dependent recurrent sHPT after TPTX+AT can easily be cured by excision of the parathyroid autotransplant under local anaesthesia. If an operation is necessary for recurrent sHPT after subtotal PTX, reexploration of the neck is mandatory in all patients including the necessity of general anaesthesia and the increased risk of recurrent laryngeal nerve palsy [48]. Therefore, in case of recurrent disease, subtotal PTX as preceding procedure is clearly inferior to TPTX+AT given equal effectiveness for the initial treatment of sHPT.

Total parathyroidectomy without autotransplantation and without routinely performed thymectomy (TPTX) may provide an alternative strategy to the currently performed procedures mainly because of the reported lower rate of recurrent sHPT of 0–4% during long-term follow up [32,36]. Patients after TPTX did not develop hypoparathyroidism [32,36] and particularly adynamic bone disease as initially expected [32,36,49-52]. Moreover, patients lacking a parathyroid remnant maintained on a noncritical calcium/phosphate product during the ongoing follow-up, compared to individuals with persisting parathyroid secretion after PTX [38].

One explanation for the absence of serious adverse events may be that thymectomy was not performed on a regular basis. The inferior parathyroid glands and the thymus derive together from the third pharyngeal pouch. Even in case of resection of all four parathyroid glands (TPTX) residual microscopic parathyroid tissue or supernumerary glands may be located in the thymus preventing the patients to develop hypoparathyroidism and its sequelae [29,40,53-56].

### Aim of the study

The objective of this trial is to compare the different outcomes of two different surgical strategies (TPTX+AT+ versus TPTX) for secondary hyperparathyroidism over a three-year follow-up period.

Reducing the risk for recurrent sHPT is an important factor for the patients and the health care system, as surgery for recurrent sHPT is associated with high costs for localization, a lesser cure-rate and a higher morbidity when compared to intial parathyroidectomy [57]. All attempt should be done to reduce the risk of its development.

Further more, TPTX without parathyroid autotransplantation and without thymectomy is associated with a reduced operating time when compared to TPTX+AT thus leading to reduced costs when compared to TPTX+AT.

### Need for this study

To date, no prospective, randomized study exists comparing TPTX to the standard surgical procedures. The existing evidence of the potential superiority of TPTX regarding the recurrence rate is flawed due to mainly methodological problems of studies with different definitions of outcomes, varying follow up periods, different surgical treatment strategies (with and without thymectomy) and their retrospective design. Therefore bias and chance are not sufficiently controlled and the results of the present studies have to be interpreted with caution.

The difference observed between the rates of recurrent sHPT of TPTX+AT and TPTX seems to be of clinical relevance. To assess the true rates of both methods, a multicentred, randomized controlled trial (MRCT) under standardized conditions is mandatory to achieve high internal as well as external validity.

Due to the existing uncertainties the calculated number of patients necessary in each treatment arm (n > 4000) makes it impossible to perform this study as a confirmatory trial.

Therefore estimates of different outcomes are performed using a pilot MRCT comparing 50 versus 50 randomized patients in order to establish a hypothesis that can be tested thereafter. This seems to be feasible and ethical.

## Methods/Design

### Objectives of the study

The objective of this study is to compare different outcomes of TPTX and TPTX+AT for sHPT over a three-year follow-up period. The information gained will be used for further clinical trials.

The primary objective of this trial is to assess a better estimate of the rates of recurrence of both methods. This shall establish a hypothesis that can be tested thereafter.

Secondary objectives are divided into those occurring intraoperative, postoperative until discharge and after discharge until 36 months postoperatively.

Intraoperative categories comprise the duration of the surgical procedures, the expertise of the responsible surgeon, and complications and findings during surgery.

Within the postoperative setting until discharge, the frequency of persistent hyperparathyroidism, the morbidity and the length of hospital stay are noted. During follow up, the frequency of persistent or recurrent sHPT, the frequency of subsequent parathyroid autotransplantation due to refractory hypoparathyroidism, the frequency of reexploration of the neck or the parathyroid autograft, the frequency of irreversible paralysis of the recurrent laryngeal nerve, the change of symptoms related to sHPT as well as the change in quality of life and finally the incidence of death are recorded.

### Trial population

Patients on long-term (>12 months) dialysis with sHPT (PTH ≥ tenfold above normal value) either with hypercalcemia (developing spontaneously or under treatment with Vitamin D) or with normocalcemia in coincidence with renal osteopathy.

### Eligibility

Detailed inclusion and exclusion criteria are specified in table 1.

**Table 1 T1:** Subject Inclusion and Exclusion Criteria

**Inclusion criteria**	**Exclusion criteria**
• Patients on long term dialysis treatment (>12 months) with sHPT	• Primary or Tertiary hyperparathyroidism (hyperparathyroidism after kidney transplantation)
• PTH ≥ tenfold above upper normal value	• Familial hyperparathyroidism(MEN I, MEN II, hereditary hyperparathyroidism)
• Age equal or greater 18 years	• History of neck explorations for thyroid/parathyroid disorders
• Informed consent	• Malignant disease of the thyroid glands
	• Bleeding disorder/coagulopathy
	• Severe psychiatric or neurologic disease
	• Drug- and/or alcohol-abuse
	• Participation in another intervention-trial with interference of intervention and outcome
	• Inability to follow the instructions given by the investigator (e.g. insufficient command of language)

Patients are screened consecutively for eligibility in all participating centres after approval of the study protocol by the local ethics committee. A contract has been signed by the Study Centre of the German Surgical Society in Heidelberg (SDGC) and the participating hospitals for correct conduction of the trial according to Good Clinical Practice. All participating surgeons performing the interventions have been instructed by detailed manuals.

### Consent

Patients who are scheduled for parathyroidectomy because of sHPT will have a pretreatment visit to give informed consent. During this visit the patient will be screened and informed about the TOPAR PILOT trial. In this conversation with the patient the study procedures, risks, benefits and data management will be clarified in detail.

### Procedures for minimizing bias and blinding

Several appropriate methods are used in order to minimize random and systematic sources of bias.

In order to achieve equal groups of patients free from systematic selection bias, an internet-based computer randomization is performed after informed consent at each centre. The main responsibility for the randomization process lies at the SDGC in Heidelberg.

The internet-based computer randomization is performed using the Randomizer for Clinical Trials 1.6.0, developed at the Institute for Medical Informatics, Statistics and Documentation at Medical University of Graz, Austria. The randomization is stratified by centres and is done to generate equal treatment groups by minimizing selection bias. Stratification for the participating clinical sites reduces bias due to centre effects. The trial is only performed in high volume centres (defined as more than 15 parathyroidectomies per year for sHPT) minimizing bias due to learning effects. No additional surgical training has to be done as the neck exploration is the same in TPTX+AT as in the standard procedure and in TPTX.

In order to obtain blinding in this trial a shame procedure would be mandatory in the TPTX group for fake autotransplantation which is in this case unethical due to the design of a non confirmatory study.

### Interventions

#### Preoperative interventions

Patients eligible to participate will be asked to give informed consent. Patients will be randomised into the following treatment groups thereafter.

Consecutively, baseline data will be documented at screening visit, including past medical history, current specific medication and current symptoms of sHPT. A quality of life questionnaire (SF-36) will be handed out preoperatively.

#### Surgical interventions

The responsible surgeon will document any particularities of the surgical intervention and the estimated number of similar operations he/she has performed so far. A standardized surgical approach to the parathyroids will be performed in both groups:

With the patients under endotracheal anesthesia and with the neck hyperextended, a Kocher's incision is made, preferably in a skin crease. The incision line should be drawn preoperatively, two fingerbreadths above the suprasternal notch when the neck of the patient is extended. The subcutaneous layer and platysm muscle is cut with electric cautery. The upper flap is raised to the upper border of the thyroid cartilage. The lower flap is mobilized to the suprasternal notch. A retractor system is used to local standards. The cervical fascia is incised in the midline. The sternothyroid and sternohyoid muscles are retracted or divided. On both sides, thyroid lobes are rotated medially, and the middle thyroid veins are divided. The lobes are retracted medially one after another and the inferior thyroid arteries and recurrent laryngeal nerves are identified.

#### TPTX Group

After mobilization of the thyroid gland, the parathyroid glands have to be identified within the cricothyroid space or in the thyrothymic tongue. Resection of all four (or more) parathyroid glands is performed, carefully avoiding any damage to the parathyroid capsules. The surgeon must change gloves to avoid seeding of parathyroid cells after preserving a part of each gland for pathology. Thymectomy on one side is only performed, if only one gland is found in the respective side or if palpation reveals a suspicious mass within the thymus.

#### TPTX+AT Group

Performance of TPTX, supplemented by bilateral routine cervical thymectomy as complete as possible.

Autotransplantation (AT): a small incision is made over the brachioradial muscle of the non-shunt-bearing forearm (alternative: muscles of the lower limb). After cutting approximately 50 mg of the most normal appearing, e.g. smallest, preferably nonnodular parathyroid gland into pieces of 1 mm^3 ^in size, 20 of these pieces are placed in single muscle pockets each of the brachioradial muscle which are closed by clips thereafter.

#### Histology procedures and crypreservation of resected specimen (both groups)

A small part of each gland has to be sent to pathology for frozen section in order to confirm organ diagnosis. The remaining parathyroid tissue will be placed in cold sterile saline solution for later cryopreservation. Cryopreservation is performed by placing cut pieces of the selected parathyroid gland into a vial containing a solution of 80% culture media, 10% patient serum and 10% dimethyl sulfoxide. The vial is then cooled to 70°C at a rate of 1°C per minute.

#### Postoperative interventions

At day of discharge from hospital, the laboratory parameters and current specific medication are documented again. Patients are asked to fill out another quality of life questionnaire (SF-36). Assessment of vocal cord function has to be documented.

After discharge a follow up visits at 6, 12, 24 and 36 months postoperatively are performed. Follow-up visits consist of a telephone call, a written questionnaire (medical history, current specific medication and specific symptoms and a quality of life questionnaire (SF-36)) to the patient, who is asked to complete it with the help of their general practitioner or nephrologists. The follow up is under the responsibility of the centres under supervision of the SDGC.

Figure 2 shows a flow-chart of the interventions.

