### Safety aspects

A small part of each gland is sent to pathology for frozen section in order to confirm organ diagnosis. The success of the intervention is assessed by perioperative monitoring of PTH and calcium recorded in the CRF. All participating centres guarantee cryopreservation of parathyroid tissue from each patient to enable possible subsequent parathyroid autotransplantation, if necessary. If postoperative persistent hypoparathyroidism refractory to medical treatment occurs, reimplantation is performed. The necessity of reimplantation is discussed and defined in each individual case by a medical clinical expert board. Therefore, clinical symptoms (e.g. repeated episodes of paraesthesia and seizures or others), the necessity and amount of medication to achieve normocalcemia and laboratory data (PTH, calcium) will be taken into consideration.

All serious adverse events (SAE) have to be reported to the principal investigator and the leading ethic committee. For the safety analysis the incidence of adverse events (AE) and SAE are analyzed. Patients may be withdrawn from the study at any time either at their own request or at the request of the principal investigator.

Safety evaluation will be done. The adverse events of both treatment groups will be demonstrated in comparison considering severity and causality. Safety interim analyses are planned each year and the independent data and safety board will follow the progress of the trial to control the safety.

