## Discussion

TOPAR PILOT is a randomized controlled multicentred pilot trial to generate high quality evidence comparing the outcomes of TPTX+AT vs. TPTX. Since secondary hyperparathyroidism is a very common disease in patients with chronic kidney failure, even a small difference in outcomes will be of clinical relevance. If TPTX proves to have no relevant disadvantages and a smaller rate of recurrent sHPT, a large scale confirmatory study will be launched to establish this approach.

Recent reports comparing TPTX+AT to TPTX were retrospective, underpowered or not designed as RCT's. No unique definition for recurrent sHPT was used to calculate the rate of recurrent sHPT. The follow up periods of former studies have often been too short and were not standardized (table 2). Therefore we will perform a follow up of each patient at 6, 12, 24 and 36 months after surgery to allow an assessment of the medium/long term effect of the different surgical treatments.

**Table 2 T2:** Rate of recurrent sHPT after TPTX or TPTX+AT

**Reference**	**TPTX+ AT n**	**TPTX n**	**Routinely performed thymectomy**	**Mean length of follow – up (months)**	**Recurrent sHPT^1 ^(%)**
Rothmund et al. 1991 [29]	20		yes	43	0
Zaraca et al. 1999 [58]	18		no, only if palpation was suspicious or parathyroid gland was missing	28	10
Walgenbach et al. 1997 [46]	67		yes	18	4.5
Walgenbach et al. 1998 [59]	86		yes	24	3.5
Henry et al.1990 [40]	152		no	30	10.5
Welk and Alix 1987 [60]	21		n.m.	33	24
Hampl et al. 1991 [37]	13		yes	33.5	76.5
Chou et al. 2002 [61]	75		n.m.	54	13.3
Bessell et al. 1993 84	42		n.m.	40	9.5
Dotzenrath et al. 2003 [62]	99		yes	51	6
Korzets et al. 1987 [63]	19		n.m.	6–60	26.3
Kinnaert et al. 2000 [31]	59		no	38	12
Tominaga et al. 1997 [39]	519		yes	36	10
				60	20
Ockert et al. 2002 [32]	11		no	38	45
		11	no	22.5	0
Kaye et al. 1993 [64]		13	n.m.	46	0
Higgins et al. 1991 [44]	34		no	72	80
		9	no	10	0
Nicholson 1996 [36]	13		no	24	16
		24	no	24	0
Saunders et al. 2005 [52]		55	no	29	4
Stracke et al. 1999 [35]		20	n.m.	20	4
Hampl et al. 1999 [65]		11	no	26	0
Ljutic D et al. 1994 [66]		43	no	104	2.3

n.m. = not mentioned

^1 ^Recurrent sHPT is defined as an increase of PTH > 5 fold above normal value after more than 6 months after initial PTX and after initial (postoperative) normalization of PTH.

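### Recurrence is defined by PTH, but the described content of the 6 to 36 month visits includes no PTH value, so the primary outcome would rest on reports rather than systematic measurement

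*Protocol article*

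**What the plan says.** - **Primary objective** (Objectives of the study): "The primary objective of this trial is to assess a better estimate of the rates of recurrence of both methods".
- **Definition of recurrence** (Discussion, footnote to Table 2): "Recurrent sHPT is defined as an increase of PTH > 5 fold above normal value after more than 6 months after initial PTX", with the further condition that this comes "after initial (postoperative) normalization of PTH". No other definition appears in the article.
- **Timing of follow-up** (Postoperative interventions): "After discharge a follow up visits at 6, 12, 24 and 36 months postoperatively are performed".
- **Content of follow-up** (same section): "Follow-up visits consist of a telephone call, a written questionnaire (medical history, current specific medication and specific symptoms", plus the SF-36. The patient fills in the forms with help from the general practitioner or nephrologist.
- **Laboratory data** (same section): laboratory parameters and vocal cord function are named for the day of discharge. Safety aspects adds "perioperative monitoring of PTH and calcium recorded in the CRF". It also says PTH and calcium are weighed case by case when reimplantation for refractory hypoparathyroidism is considered.
- **A related secondary outcome** (Objectives of the study), listed among the items recorded during follow-up: "the frequency of irreversible paralysis of the recurrent laryngeal nerve".

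**The concern.** The endpoint needs a laboratory value at a time when the described visits do not collect one. Laboratory data are named at discharge and left out of the follow-up list a few lines later, so the gap looks like more than loose wording.

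The pilot exists to supply recurrence rates on which a confirmatory trial can be built. If recurrence is recorded only when symptoms, a physician's suspicion or a routine test brings it to notice, patients with a raised PTH and no complaint can be counted as free of recurrence. Treatment is not blinded, so the prompt to test may also differ by arm. Sections Need for this study and Discussion fault earlier studies for differing definitions and unstandardised follow-up. Visits without the defining measurement would leave part of that weakness in place.

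**Working it through.** The plan gives no figure for ascertainment of recurrence, so there is none to reproduce. The calculation under Number of patients needed concerns a hypothetical confirmatory trial and does not enter here. The check sets each element of the definition against the data the visible text says will be collected.

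1. **Initial normalisation of PTH.** Perioperative PTH and the discharge laboratory values can supply this.
2. **PTH more than five times normal.** This needs a PTH value and the reference limit of the assay used. Neither is listed for 6, 12, 24 or 36 months.
3. **More than six months after surgery.** Discharge values cannot qualify. A value from a visit at exactly six months does not qualify by itself either. The scheduled visits that could are those at 12, 24 and 36 months, and their described content has no laboratory item.
4. **Other PTH data after discharge.** The only such use in the text is the expert board's case-by-case review for reimplantation. It is triggered by hypoparathyroidism, the opposite condition, so it does not capture recurrence.

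Elements 2 and 3 therefore have no scheduled data source in the visible text.

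**Scale.** Inputs are 50 patients per arm (Number of patients needed) and the published recurrence rates the article cites under Current treatment options: 10% to 12% for the standard procedures and 0% to 4% for TPTX.

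- Expected recurrences with TPTX+AT: 50 × 0.10 = 5 to 50 × 0.12 = 6.
- Expected recurrences with TPTX: 50 × 0 = 0 to 50 × 0.04 = 2.
- Effect of one missed recurrence: 1/50 = 2 percentage points. For example, 5/50 = 10% becomes 4/50 = 8%.
- Exact (Clopper-Pearson) 95% confidence intervals: 3.3% to 21.8% for 5/50, and 0% to 7.1% for 0/50.

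The intervals are wide, but they describe sampling error only. A missed recurrence always pulls the estimate down, and the interval does not allow for it.

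**Could ascertainment differ by arm?** The section on minimizing bias and blinding explains why patients are not blinded. Current treatment options places about 80% of recurrences after TPTX+AT at the graft, and the legend of Figure 1 describes such a graft as a lump under the scar. A visible sign can prompt a PTH test in one arm only. Conversely, worry about hypoparathyroidism after TPTX could prompt tests in the other arm. The documents make a difference possible but fix neither its direction nor its size.

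**Nerve paralysis.** Irreversibility requires a later examination. Vocal cord documentation is stated only at discharge, so the described data cannot separate a transient palsy from a permanent one.

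**The case against.** The strongest reply is that the whole schedule is not visible. The section on postoperative interventions ends by pointing to Figure 2, whose legend says it covers all interventions, and that figure is not shown. The Discussion says that data assessment and documentation of outcome measures are specified in advance in the trial protocol, which is not shown either. Laboratory tests per visit could stand in both. This holds, and it limits confidence. It does not remove the point, because the article does more than stay silent: it says what the visits consist of, and that content lacks the defining variable. If Figure 2 or the full protocol schedules PTH, this sentence still has to be reconciled with them.

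Second, the definition stands in a footnote to a literature table, and Methods does not adopt it. Reading it as the trial's endpoint is an inference, though a fair one since no other definition is given.

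Third, follow-up is not left to chance. A physician helps with the forms, there is a telephone call, and the centres are responsible under supervision of the study centre. Routine PTH values may well be reported. But the text does not ask for them and fixes no date, assay or reference limit, so capture would be neither complete nor uniform.

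**Conclusion.** The point stands in a limited form. In the visible text, the described follow-up does not supply the measurement that the only definition of recurrence requires. Ascertainment of the primary outcome would be incomplete and unstandardised, with possible differences by arm. Each missed recurrence costs 2 percentage points, against expected counts of about 5 to 6 and 0 to 2. This rests on two assumptions: that the Table 2 footnote is the intended endpoint, and that the unseen Figure 2 and full protocol add no PTH schedule.

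Three stronger readings are not supported:

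- A reader might infer that recurrence cannot be determined at all in this trial. That goes too far, given the unseen documents and the physician's part in completing the questionnaire.
- A reader might infer a bias of a given size, or one that favours TPTX. The documents contain no detection rates, so any such figure would be invented.
- A reader might infer, because "a small incision is made over the brachioradial muscle of the non-shunt-bearing forearm", that samples from that arm would show falsely high PTH. The article does not say where blood is drawn or what such a sample would show, and it also allows a graft in the lower limb. The point would rest on outside knowledge.

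**What to change.** 1. State the recurrence definition in Methods as the trial endpoint, including the condition of initial normalisation.
2. In Postoperative interventions, record intact PTH at each follow-up visit, with the date and the assay's upper normal limit, transcribed from the treating dialysis unit. Bring Figure 2 and the full protocol into line.
3. Classify recurrence by that definition from all PTH values later than six months after surgery. Include values obtained between visits and those preceding a reexploration of the neck or autograft for recurrent disease. A rule limited to scheduled values could miss patients reoperated between visits, since PTH may have fallen by the next one. Such misses would fall mainly in the TPTX+AT arm, where the article describes graft excision as an easy cure.
4. State that the six-month value alone cannot establish recurrence.
5. For patients with a palsy at discharge, record the later vocal cord result before the palsy is counted as irreversible.

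The cost is a few sentences of protocol text, minor CRF work and at most 4 × 100 = 400 transcribed laboratory values, plus the later vocal cord result for the patients concerned.
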